**Fig. 2 Fig2:**
[figure not shown]
Flow chart representing study process

### Participant timeline

Participant timeline was developed according to the SPIRIT guideline and is presented in Table 3.

**Table 3 Tab3:** Timeline of screening, recruitment, randomization, interventions, and assessments

Time point	Study period		
	0 week (w)	4 w	Closeout (4 w)
Enrollment			
Eligibility screen	x		
Informed consent	x		
Allocation	x		
Intervention			
Experimental group	x	x	
Control group	x	x	
Assessments			
Demographics	x		
FMA-UE	x	x	
WMFT	x	x	
MBI	x	x	

*FAM-UE* Fugl-Meyer Assessment-upper extremity, *WMFT* Wolf Motor Function Test, *MBI* Modified Barthel Index

Rehabilitation interventions are crucial during the first 4 weeks post-stroke as it is a critical time for neural plasticity and recovery [17]. Therefore, the present study will be initiated within 48 to 72 h of patient admission in the acute care unit and will be continued for 4 weeks following the initial assessment. Following admission to an acute stroke unit, screening and informed consent and baseline outcome assessments will be completed within 48 to 72 h. The mirror therapy education will commence immediately after the baseline assessment and end in 4 weeks.

### Statistical analysis

#### Data analysis

Data will be analyzed using the SPSS software version 23. Demographic characteristics and baseline scores will be compared using the independent *t*-test and the chi-squared test for continuous variables (such as age and time since stroke) and dichotomous variables (gender, dominance, affected side, and type of lesion), respectively. A two-way repeated analysis of variance (ANOVA) with time and group effects will be used to analyze between-group differences. We will administer both intention-to-treat and per-protocol analyses to determine the effectiveness of the proposed intervention [27]. The level of significance will be set at *P* < 0.05. Patients will be considered as being compliant if they perform at least 80% of the original MT protocol. The compliance will be reported using the four ways recommended by Hawley-Hague et al. (i.e., completion, attendance, duration adherence, and intensity adherence) [28]. In addition, CONSORT will be used to report this RCT to facilitate reading and quality assessment.

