**Study outcome:**

The primary outcome measure will be upper extremity function that will be measured using the Fugl-Meyer Assessment scale and the Wolf Motor Function Test. The secondary outcome measure will be behaviors related to ADL as estimated using the Modified Barthel Index. Outcome measures will be assessed at baseline and at 4 weeks post-rehabilitation intervention/MT.

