**Results:**

A two-way repeated analysis of variance (ANOVA) with time and group effects will be used to analyze between-group differences. The level of significance will be set at *P* < 0.05.

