### Group assignment

#### Sample size estimates

The sample size and effect size were calculated based on a previously published study [24], using the G* power software. A sample of 18 will be required in each group to detect a difference in the primary outcome measure (FMA-UE) with an effect size (Cohen’s d) of 1.15 and a statistical power of 0.80 at a one-sided type one error of 0.05.

Based on the above calculation, a total of 36 patients will be recruited and assigned to the MT (n = 18) or control group (n =18) using a random sampling method. Randomization will be done prior to the baseline assessment with a statistical software program that generates this sequence. Random numbers will be assigned according to the order of patients’ admission to the hospital. To *conceal allocation*, random group allotment will be managed by a social worker who will not be involved in the assessment or intervention to minimize the confounding and contamination. Refer to Fig. 1 for the study process.

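### The planned repeated-measures ANOVA does not name the group-by-time term, the only one that isolates the treatment effect here; ANCOVA on the baseline score would settle this at almost no cost

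*Protocol article*

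**What the plan says.** The Data analysis section of the protocol article states: "A two-way repeated analysis of variance (ANOVA) with time and group effects will be used to analyze between-group differences". The Results paragraph of the abstract repeats the sentence. No other efficacy test is described, and neither place mentions an interaction, a change score or a baseline covariate. Data analysis uses the baseline scores only to compare the groups at entry.

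There are two measurement times: "Outcome measures will be assessed at baseline and at 4 weeks post-rehabilitation intervention/MT". The first precedes treatment, because under Participant timeline "The mirror therapy education will commence immediately after the baseline assessment and end in 4 weeks".

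Sample size estimates plans 18 patients per group for FMA-UE, with a Cohen's d "of 1.15 and a statistical power of 0.80 at a one-sided type one error of 0.05".

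**The concern.** A two-way ANOVA with group and time as factors yields three tests. With one pre-treatment and one post-treatment measurement, they answer different questions:

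- The time effect is the average change in the two arms together. It says nothing about what mirror therapy adds.
- The group effect is the difference between arms averaged over both times. Randomisation makes the expected baseline difference zero, so this average dilutes the treatment effect.
- The group-by-time effect is the difference between arms in change from baseline. This is the treatment contrast.

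The sentence names time and group and ties them to between-group differences, but leaves out the third. Someone running the analysis could report the group line as the result. The wording also leaves room to choose among the P values once the data are in. Apart from that, the plan collects a baseline score for every outcome and does not use it for adjustment, where it would sharpen the comparison.

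**Working it through.** **Inputs from the protocol article.** d = 1.15, 18 per group, 80% power at one-sided 0.05 (Sample size estimates); two time points (abstract, Study outcome); treatment starts after baseline (Participant timeline); significance at P < 0.05, sidedness not stated (Data analysis). An ANOVA F test is non-directional, so results are shown two-sided and, to match the sample size basis, one-sided.

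**Assumptions not in the document.** Equal SDs at the two times; d standardised by the SD of a single 4-week score; correlation rho between baseline and 4-week scores of 0.5 to 0.8.

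**The plan's own figure.** A two-sample t test with d = 1.15, one-sided 0.05 and 80% power needs 11 per group, not 18. Eighteen per group corresponds to 95% power. That mismatch is a separate matter, and n = 18 is taken as given below. At 18 per group, a simple comparison of 4-week scores has 96% power one-sided and 92% two-sided.

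**Size of each contrast.** Let delta be the true 4-week difference.

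- Group main effect: expected value (0 + delta)/2 = delta/2. The mean of a patient's two scores has variance (1 + rho)/2 in SD² units, so the standardised effect is (d/2)/sqrt((1 + rho)/2). At rho 0.5 this is 0.575/sqrt(0.75) = 0.66; at rho 0.8 it is 0.575/sqrt(0.90) = 0.61.
- Group-by-time (change score): expected value delta, variance 2(1 - rho), standardised effect d/sqrt(2(1 - rho)). At rho 0.5 this is 1.15/1 = 1.15; at rho 0.8 it is 1.15/sqrt(0.40) = 1.82.
- ANCOVA: expected value delta, residual variance 1 - rho², standardised effect d/sqrt(1 - rho²). At rho 0.5 this is 1.15/sqrt(0.75) = 1.33; at rho 0.8 it is 1.15/sqrt(0.36) = 1.92.

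**Power** (noncentral t, 18 per group, alpha 0.05, one degree of freedom removed for ANCOVA):

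| Test | Sides | rho 0.5 | rho 0.7 | rho 0.8 |
|---|---|---|---|---|
| Group main effect | two | 49% | 44% | 42% |
| Group main effect | one | 62% | 58% | 56% |
| Group-by-time | two | 92% | 99% | >99.9% |
| ANCOVA | two | 97% | 99.7% | >99.9% |

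Over the wider range of rho from 0 to 0.9, the group main effect has 66% down to 41% power two-sided and 77% down to 54% one-sided, so it is below 80% throughout. Group-by-time is weaker at low correlation: 81% two-sided at rho 0.3, against 94% for ANCOVA.

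**Check by simulation** (20,000 trials at each rho, true difference 1.15). At rho 0.5 the group main effect averaged 0.576 and was significant in 49% of trials; the change contrast averaged 1.154 and was significant in 92%. At rho 0.7 the averages were 0.577 and 1.150, significant in 44% and 99%.

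**Change score against ANCOVA.** The variance ratio is 2(1 - rho)/(1 - rho²) = 2/(1 + rho): 1.33 at rho 0.5, 1.18 at rho 0.7 and 1.11 at rho 0.8.

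**The case against.** A reader might infer that the plan tests the group main effect, and therefore targets the wrong quantity and misses its 80% power. The document does not establish this. The phrase about time and group effects can just as well list the two factors of a mixed ANOVA. Such a model ordinarily yields group-by-time as well, and nothing in the article excludes that term or makes the group main effect the primary test. A condensed article may also leave the decisive contrast to a fuller document that is not shown. On this reading nothing is halved, the change-score contrast is a valid estimate of the treatment effect, and power at d = 1.15 exceeds 80% across the assumed range.

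Two further cautions stand. The planned 80% is one-sided, so the like-for-like figures for the group main effect are 62% to 56%, not 49% to 42%. Also, neither rho nor the SD behind d is given. If d was standardised on change scores, group-by-time has 92% two-sided power whatever rho is, and the main-effect figures above no longer apply.

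Preferring ANCOVA to a valid change-score test is advice on efficiency, not the correction of an error. At d = 1.15 it adds about 5 points of power at rho 0.5 and almost nothing at rho 0.8.

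The objection does not remove the ambiguity. The only efficacy sentence, given twice, names two effects that do not isolate treatment and omits the one that does.

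**Conclusion.** The point holds as an ambiguity with a simple remedy and should be fixed; it does not show that the trial will test the wrong quantity. If the group main effect were read as the treatment test, the estimate would be half the true effect. That follows from the two-time-point design and does not depend on rho. Power would fall below the planned 80%, one-sided or two-sided. If group-by-time is intended, the analysis is sound and adequately powered at the planning effect for rho 0.5 to 0.8, and what is lost is the 1.11 to 1.33 variance factor relative to ANCOVA. The power figures and the variance factor rest on the assumed rho and equal SDs; the power figures also rest on d being scaled by the 4-week SD. ANCOVA is the better choice on either reading.

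**What to change.** In the abstract and in Data analysis, replace the ANOVA sentence with wording such as: The primary analysis is an ANCOVA of the 4-week FMA-UE score on randomised group with baseline FMA-UE as covariate, reporting the adjusted mean difference with its 95% confidence interval; WMFT and MBI are analysed in the same way, each with its own baseline score. A repeated-measures ANOVA may stay as a supportive analysis, with a statement that it is interpreted only through group-by-time.

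The cost is one degree of freedom and a change of wording. The baseline scores are already collected, and no visit, patient or measurement is added. Trial status reports no patients recruited at its stated date, so at that point the change could be made before any outcome was seen.

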### Limitations

A limitation of this study is having two primary outcome measures which affects the power of the study. However, we decided to include both the outcome measures as we are interested in exploring the effectiveness of MT in improving motor impairment and motor function.

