### Outcome measures and data collection

The primary outcome measures of interest are the level of upper limb motor impairment and functional performance. These variables will be measured using the Fugl-Meyer Assessment-upper extremity (FMA-UE) and the Wolf Motor Function Test (WMFT), respectively. Both FMA-UE and WMFT are reliable and valid outcome measures and are used consistently in MT research [25]. Moreover, the Stroke Edge Task Force of the Academy of Neurological Physical Therapy (American Physical Therapy Association) recommends FMA-UE and WMFT for patients who have had a stroke and who are undergoing acute care [26]. The secondary outcome measure will be ADL measured by the Modified Barthel Index (MBI), a reliable and valid tool for assessing ADL in stroke survivors and used in MT research.

A physiotherapist will assess the above outcome measures twice: (1) pre-test assessment at the beginning of the trial and (2) post-test assessment at the end of the trial. Before the study, the assessor will be trained in assessing all outcome measures and will be tested with two patients to assure standardization. The assessors will be trained by one of the investigators of this study (VR) who is a physiotherapist specialized in stroke rehabilitation and experienced in administering the above outcome measures. In addition, demographic characteristics, such as age, gender, handedness, Alpha-FIM score, Brunnstrom stages of motor recovery, type of lesion, side of hemiplegia, and the onset of stroke, will be collected during the initial assessments (Fig. 2).

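### FMA-UE and WMFT are both primary under one 0.05 threshold with no stated order, split or success rule: type I error is about 7–10% if either suffices, and joint power is uncalculated if both must succeed

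*Protocol article*

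**What the plan says.** The number of primary outcomes differs between sections of the protocol article.

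- **Outcome measures and data collection** uses the plural: "The primary outcome measures of interest are the level of upper limb motor impairment and functional performance", assessed by FMA-UE and WMFT respectively. The abstract also puts both scales under its primary outcome: "measured using the Fugl-Meyer Assessment scale and the Wolf Motor Function Test".
- **Sample size estimates** uses the singular. The 18 per group are required "to detect a difference in the primary outcome measure (FMA-UE"), with a Cohen's d "of 1.15 and a statistical power of 0.80 at a one-sided type one error of 0.05". WMFT has no calculation.
- **Data analysis** gives one threshold for everything: "The level of significance will be set at *P* < 0.05". It mentions no order of testing, division of alpha or sidedness, and does not say whether success needs one outcome or both.
- **Limitations** takes up the design choice directly: "A limitation of this study is having two primary outcome measures which affects the power of the study". The reason given for keeping both is interest in impairment and in function. Type I error is not mentioned.

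**The concern.** As the plan is written, a second primary outcome takes no power from either test. Alpha is not divided, and the sample size rests on FMA-UE alone. Power becomes a cost only if alpha is split or if both outcomes must succeed, and the article states neither.

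Followed as written, the plan lets either scale be claimed at 5%. A significant WMFT result alone, on an outcome with no stated power basis, could be presented as a primary success. The chance of at least one false claim would then exceed 5%. If the intention is that both must succeed, the 80% power quoted for FMA-UE does not describe the trial's chance of success. Each reading leaves something unaddressed, and the reader cannot tell which applies.

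**Working it through.** **Inputs from the article.** Two primary outcomes; threshold 0.05 (Data analysis); 18 per group, d = 1.15, power 0.80, one-sided alpha 0.05, FMA-UE only (Sample size estimates).

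**Input not in the article.** The correlation r between the two test statistics. A range is shown.

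**1. The article's own sample size.** By the normal approximation, n per group = 2(z₀.₉₅ + z₀.₈₀)²/d² = 2(1.645 + 0.842)²/1.15² ≈ 9.4, so 10. The noncentral t gives 10.1, so 11. The stated 18 is not reproduced. With 18 per group and d = 1.15, one-sided power is 95.9%. Power of 80% at 18 per group and one-sided 0.05 corresponds to d of about 0.85. This matters in step 4.

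**2. If either outcome suffices.** For independent tests, the family-wise error is 1 − (1 − 0.05)² = 0.0975; the upper bound is 0.05 + 0.05 = 0.10. For correlated tests, two-sided, it is 1 − P(|Z₁| < 1.96, |Z₂| < 1.96) under a bivariate normal with correlation r. One-sided, it is 1 − P(Z₁ < 1.645, Z₂ < 1.645).

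| r (assumed) | Two-sided | One-sided |
|---|---|---|
| 0 | 9.75% | 9.75% |
| 0.5 | 9.1% | 8.8% |
| 0.7 | 8.3% | 8.0% |
| 0.8 | 7.8% | 7.5% |
| 0.9 | 7.0% | 6.8% |

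**3. If both must be significant.** A false claim of joint success requires rejecting at least one true null hypothesis at 0.05, so type I error is at most 5%. The cost moves to power. If each outcome has 80% power, joint power is 0.80 × 0.80 = 64% at r = 0, 69% at r = 0.5, 73% at r = 0.8 and 75% at r = 0.9. If WMFT also had d = 1.15 (an assumption), each test would have 91.8% power at two-sided 0.05, and joint power would be 86% to 89% for r from 0.5 to 0.9.

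**4. Power cost of splitting alpha.** Two-sided noncentral-t power per outcome, 18 per group:

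| d | Alpha 0.05 | Alpha 0.025 |
|---|---|---|
| 1.15 (sample size section) | 91.8% | 86.0% |
| 0.85 (gives the stated 80% one-sided) | 70% | 58% |
| 0.47 (pooled effect in the Critical review section) | 28% | 19% |

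A fixed sequence starting with FMA-UE pays none of this on FMA-UE, which keeps the full 0.05 whatever the true effect.

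**The case against.** The strongest reply is that the article states no either-outcome rule. It assigns each scale its own construct and speaks of exploring both, so separate claims for impairment and function are a possible reading, and so is a requirement that both succeed. Under that last reading power is the right concern and the Limitations sentence is correct. It is also correct if alpha is adjusted. This stands: the sentence is incomplete, not false.

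A reader might infer that the trial's true false-positive rate is nearly double the nominal 5%. The documents do not support that. The inflation exists only if either outcome suffices, and its size depends on a correlation that the article does not give; at 0.8 it is about 1.6 times nominal (7.8/5). A reader might also infer from d = 1.15 that splitting alpha costs little. That relies on a set of d, n and power that does not reproduce. At d of about 0.85 the loss is from 70% to 58%.

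Finally, a multiplicity procedure may sit in an analysis plan that is not shown, and a threshold of 0.05 is compatible with Holm at an overall 0.05. Absence alone would therefore be no finding. What remains is in the visible text: one primary in the sample size section against two elsewhere, a single unqualified threshold, and a limitation that addresses this very choice yet names only one of its consequences.

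**Conclusion.** The point holds in conditional form. The article disagrees with itself on the number of primary outcomes, and fixes one 0.05 threshold without a stated order, split or success rule.

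- If either outcome suffices, family-wise type I error is about 7–10% for correlations from 0 to 0.9.
- If both are required, type I error is at most 5%, and joint power is the missing figure.

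The result rests on an assumed correlation and, for the first branch, on an either-outcome rule that the text permits but does not state. Sidedness is also unsettled: the sample size uses one-sided 0.05 and the analysis section names none. It changes the error figures little (7.0% against 6.8% at r = 0.9). The change should be made, because the present text lets a lone result on the unsized outcome be claimed at 5%.

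**What to change.** **Preferred.** Name FMA-UE, the outcome the trial is sized on, as the single primary and test it at the full 0.05. Test WMFT next, also at 0.05, only if FMA-UE is significant. The Modified Barthel Index stays secondary. This holds the family-wise error for the two scales at 5% and leaves FMA-UE power unchanged.

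**If both must stay primary.** Either use Holm at an overall 0.05 (smaller p-value against 0.025 and, if that is met, the larger against 0.05), or state that both must be significant and report joint power with its assumed WMFT effect and correlation.

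**In either case.** Make the outcome, sample size and analysis sections agree on the number of primaries. State the same sidedness in the sample size and analysis sections. Amend the limitation to mention type I error where either outcome suffices.

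**Cost.** No new data or procedures. The authors chose to keep both outcomes primary, so the preferred option changes a deliberate decision and needs a protocol amendment, plus a registry update if both are listed there (the record is not shown). The Trial status section reports no patients recruited at its date, so on that footing the rule could be set before any data exist. The small downside is that WMFT cannot be claimed as confirmatory if FMA-UE fails.

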## Safety and adverse event monitoring

A data safety monitoring board will be notified outlining adverse events that occur from this study, from baseline assessment through to completion of the final evaluation.

## Stopping rules and early termination

Participants will be removed from the study if they want to withdraw themselves from the study. Participants’ data will be removed and will not be included for analysis if they request the withdrawal of their data before entering it for data analysis.

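### The promised ITT analysis, run as the named two-time-point repeated-measures ANOVA, covers only patients with both scores, and the withdrawal rule does not secure the 4-week score

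*Protocol article*

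**What the plan says.** Four statements in the protocol article bear on this point.

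- **Analysis sets** (Data analysis): "We will administer both intention-to-treat and per-protocol analyses to determine the effectiveness of the proposed intervention".
- **Method** (Data analysis): "A two-way repeated analysis of variance (ANOVA) with time and group effects will be used to analyze between-group differences". The software is SPSS 23. No other between-group method is named.
- **Assessments** (Outcome measures and data collection): "A physiotherapist will assess the above outcome measures twice", before the intervention and at the end. Table 3 places these at week 0 and week 4.
- **Withdrawal** (Stopping rules and early termination): "Participants will be removed from the study if they want to withdraw themselves from the study". The next sentence deals with data: they "will not be included for analysis if they request the withdrawal of their data before entering it for data analysis".

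In addition, under Sample size estimates, "Randomization will be done prior to the baseline assessment". A patient can therefore be randomised and leave before any score exists. The section recruits the calculated 36 and states no allowance for dropout.

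**The concern.** An intention-to-treat comparison keeps every randomised patient in the assigned arm. Here the method and the withdrawal rule together work against that. The ANOVA needs both scores, and a patient removed from the study before week 4 will normally not have the second one. The rule does not distinguish a patient who wants to stop the exercises from one who refuses further assessment.

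The trial is open-label, and only the MT arm has an extra 30 minutes of self-administered work on 5 days a week for 4 weeks, with a logbook (Interventions). Unequal loss between the arms is therefore plausible, although nothing in the article shows that it will occur. If MT patients who are tired or doing badly leave more often, those who remain look better than the arm as randomised, and the effect of MT is overstated.

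**Working it through.** **1. The planned size.** Inputs (Sample size estimates): d = 1.15, power 0.80, one-sided alpha 0.05, 18 per group. A two-sample t-test with these inputs needs 10.1, so 11 per group (13 if two-sided). The stated 18 does not reproduce at power 0.80; it matches power 0.95 (17.1, rounded up to 18). That is a separate matter, but it explains why power survives dropout below.

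**2. What the ANOVA estimates.** With two time points, the group-by-time test is equivalent to a two-sample t-test on change, week 4 minus baseline. Change is undefined if either score is missing, so the patient drops out of the analysis.

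**3. Plausible loss.** Only two of the five earlier trials in Table 2 report dropouts: 1/26 = 4% and 12/48 = 25%.

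**4. Power.** At 25% loss over both arms, 36 x 0.75 = 27 are analysed (14 and 13).

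| Analysed | Two-sided power at d = 1.15 | One-sided power | d detectable, two-sided, 80% power |
|---|---|---|---|
| 36 | 0.92 | 0.96 | 0.96 |
| 27 | 0.82 | 0.90 | 1.12 |

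Even at the upper documented rate, power stays above 0.80 at the design effect.

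**5. Bias from loss that depends on outcome.** This is a different scenario: loss in the MT arm only, leaving about 36 - 0.25 x 18 = 31.5 patients. If lost patients would have done worse than retained ones by a given gap, then

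bias = share lost x gap.

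- Gap 0.3 SD: 0.25 x 0.3 = 0.075, about 0.08 SD.
- Gap 1.0 SD: 0.25 x 1.0 = 0.25 SD.

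Both favour MT. Against the pooled SMD of 0.47 quoted in the Critical review, they are 0.075/0.47 = 16% and 0.25/0.47 = 53%. As an outer limit, losing exactly the worst-scoring quarter of the MT arm gives 0.43 SD. The share, the restriction to one arm and the gap are all assumptions.

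**6. Bias from loss that depends on baseline.** If MT patients with low baseline scores are lost, the baseline mean of those who remain rises by some shift s. With equal SDs and baseline-to-week-4 correlation r (assumed), the change-score comparison is biased by -(1 - r) x s. Losing the lowest fifth gives s = 0.35 SD:

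- r = 0.5: -0.5 x 0.35 = -0.18 SD.
- r = 0.8: -0.2 x 0.35 = -0.07 SD.

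This bias runs against MT, so the direction of any overall bias cannot be fixed in advance. Simulations with 4 of 18 MT patients lost by low baseline gave biases of 0.05 to 0.17 SD in size for the change-score analysis and essentially none for a baseline-adjusted one, with no material loss of precision.

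**7. What a model can and cannot repair.** With two time points, a patient with a baseline score only carries no information on the week-4 difference. A likelihood model with a common baseline mean, fitted to simulated data on 36 patients, gave the same point estimate as ANCOVA on patients with both scores (for example 0.8592 from each). Imputing from baseline alone adds nothing either. Baseline adjustment therefore deals with step 6 but not step 5.

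**The case against.** The strongest reply is that the article is a condensed protocol. Definition of the ITT set and handling of missing scores are commonly left to the full protocol or the SAP, and an ANOVA can be run on imputed data. That is fair, and the lack of an imputation paragraph is not the point here. The article does, however, commit to a method that drops incomplete cases and to a withdrawal rule that governs which scores are collected. A later analysis document cannot recover scores that were never sought.

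Four stronger readings are tempting, and the article does not support them.

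- **That data from everyone who withdraws are discarded.** The second withdrawal sentence limits deletion to an explicit request made before data entry.
- **That ITT collapses into per-protocol.** Patients below the 80% compliance threshold who are assessed at week 4 stay in the ITT analysis. The restriction is to patients with both scores, not to compliant ones.
- **That the protocol's own review found this flaw in earlier trials.** Table 2 rates all five as high risk for attrition bias, but its footnote equates high risk with non-reporting. It does not judge a withdrawal rule or an analysis method.
- **That 25% loss should be expected.** It is the higher of two reported rates, and this trial follows patients for 4 weeks within one hospital.

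**Conclusion.** The concern holds in a limited form. If the article is followed as written, the analysis called ITT is an analysis of patients with both assessments, and nothing in it secures the 4-week score of a patient who stops taking part. This should be corrected, but it is not evidence that the result will be biased.

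Power is not at issue at the documented dropout rates. The issue is bias if loss differs by arm. Its size is unknown: illustratively 0.08 to 0.25 SD in favour of MT under the MT-only loss and gap assumed above, and it could run the other way if loss follows low baseline scores. At the lower documented rate of 4%, the same formula gives at most 0.04 x 1.0 = 0.04 SD.

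**What to change.** 1. **Withdrawal wording.** Separate three events: stopping the MT exercises, leaving follow-up, and asking for data to be withdrawn. State that the 4-week assessment is sought from every randomised patient who has not withdrawn consent to follow-up. Keep the existing right to data withdrawal. Report the count of each event by arm, including patients lost between randomisation and baseline.
2. **ITT method.** Replace the repeated-measures ANOVA with ANCOVA of the week-4 score on randomised arm and baseline, or the equivalent likelihood model with a common baseline mean. This removes bias from baseline-dependent loss. With complete data its variance is about (1 + r)/2 times that of the change-score analysis: 0.75 at r = 0.5 and 0.90 at r = 0.8. It does not remove bias from outcome-dependent loss, and the plan should say so.
3. **Sensitivity analysis.** For that remaining bias, add one analysis in which missing MT-arm week-4 scores are set progressively worse, for example by 0 to 1.0 SD, and report where the conclusion changes.

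The cost is wording and a little more analysis, plus the effort of seeking week-4 scores from patients who have stopped exercising. Trial status reports no patients recruited at the time of writing, so on that information the change could precede enrolment.
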